### *Study schedule (see *Table 1* for details)*

**Table 1 Tab1:** Timeline of assessments

Assessment/form	**Screening**		**Treatment (weeks 1–4)**				
	Pre-screen	Screen	Baseline	Days 2–28			
			Week 1^a^ (D1)	Week 2^a^ (days 8–14)	Week 3^a^ (days 15–21)	Week 4^a^ (days 22–27)	Final assessment (day 28) within 7 days of last treatment
Pre-screening	*√*						
Eligibility, consent & registration		*√*					
Current MA/substance use & MA/substance use history add treatment history		√					
Medical & mental health history (incl. contraindications) and examination (medical and mental health)		*√*					
General health assessment							*√*
Concomitant medications		*√*	*√*				
Medical protocol: RMT calculation			*√*				
Socio-demographics, participant education & treatment adherence			*√*				
TMS—treatment safety screening assessments			*3*	*3*	*3*	*3*	
Study counselling (both arms)			√	√	√	√	
Vital signs			√	√	√	√	√
Adverse event log			*√*	*√*	*√*	√	√
Urine sample (for UDS)		*√*	*√*		*√*		√
Pregnancy test (where applicable)		*√*					
Timeline Follow Back (MA use only)			*√*	*√*	*√*	√	√
MA craving visual analog scale (VAS)			*√*	*√*	*√*	√	√
MA cue-exposure paradigm & craving			*√*				√
Australian Treatment Outcome Profile (ATOP)			*√*				√
Mental health (DASS-21)			*√*				√
Cognitive testing (Go/No-Go)			*√*				√
Treatment experience							√

^a^These assessments are done at the first session of the week

The study doctors will establish RMT and set the TMS parameters for each participant and conduct the first treatment session as per the participant’s randomly assigned treatment. The study doctor (or delegate certified in TMS) will provide up to three sessions per week, as per the participant’s randomly assigned treatment. The study doctor will review the patient at the conclusion of the study treatments. Final study assessments will be conducted at the end of treatment. A participant will be defined as having completed the study once they have completed their week 4 post-treatment follow-up assessment or if they are prematurely withdrawn from the entire study (i.e. treatment and research visits).

Task-based functional magnetic resonance imaging (fMRI) will be done at baseline and end of treatment for those who opt-in to a neuroimaging sub-study. Scanning is conducted while cue reactivity and the Go/No-go tasks are undertaken. Simultaneous physiological monitoring (e.g. heart rate in and out of the scanner) will also be performed. Brain areas of interest include those involved in the reward, craving and cognitive control associated pathways, i.e. the cortico-limbic striatal systems. The neuroimaging procedures and assessments are contained in a sub-study protocol that will be published separately.

Participants will be advised at the time of consenting that the study treatment and counselling will not be available after the study period (end of week 4 of treatment). Participants requesting a referral for the continuation of psychosocial counselling will be provided referral options.

Participants who withdraw from the TMS component of the study will be invited to continue completing the research component of the study. Participants may be withdrawn involuntarily by the investigator (or delegate) if they meet the following criteria: participant experiences a severe or serious adverse event, thought to be related to the study device, which is not resolving, or they miss more than 6 (of 12) study TMS sessions. Participants have the option to stop treatment or revoke their consent at any time without giving a reason and no further information would be collected from the participant for the purpose of the trial.

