**Methods:**

Thirty participants meeting the criteria for moderate to severe MA use disorder will be recruited in community drug and alcohol treatment settings and randomised to receive active TMS or sham (control) intervention. The treatment is intermittent TBS (iTBS) applied to the left dorsolateral prefrontal cortex (DLPFC), then continuous TBS (cTBS) to the left orbitofrontal cortex (OFC). Twelve sessions are administered over 4 weeks with opt-in weekly standardized cognitive behaviour therapy (CBT) counselling and a neuroimaging sub-study offered to participants. Primary outcomes are feasibility measures including recruitment, retention and acceptability of the intervention. Secondary outcomes include monitoring of safety and preliminary efficacy data including changes in substance use, cravings (cue reactivity) and cognition (response inhibition).

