Following this, cTBS will be delivered at the left OFC: One train of cTBS will be applied over the left frontal pole (Fp1) (3 pulses of 50-Hz bursts applied at 5 Hz, 15 pulses/s, 600 pulses/train; 100% RMT). During the cTBS procedure, the amplifier output will be escalated during the first train (over 30 s) from 70 to 100% RMT to enhance tolerability. For clients who experience discomfort and are not able to comfortably tolerate this intensity, the level will progressively be decreased until a comfortable intensity is reached. For both iTBS and cTBS, participants will be withdrawn if they are unable to tolerate treatment at 70% of the RMT at the end of the third day of treatment.

Three sessions of iTBS followed by cTBS will be administered with a 10-min break between the first, second and third sessions. This interval and frequency were determined based on studies showing accelerated multiple iTBS cycles delivered with an interval between each within a day as safe and efficacious [28, 29]. This was also supported by the expert opinion of study investigators with extensive TMS research experience. Treatment will be provided on 3 days of the week for a total of 4 weeks (12 sessions or days of treatment in 28 days).

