### Outcome measures

Feasibility will be assessed by recording the number of study referrals, the proportion of those who are deemed eligible and consented and their attendance and completion of scheduled treatments. A semi-structured questionnaire of patient experience will be administered post-treatment. Safety is monitored by the recording of all adverse events.

The preliminary efficacy of TMS on substance use will be determined by changes in self-reported substance use, collected using the Timeline Follow Back for MA use (a validated tool used to recall the previous 28 days of substance use) and the Australian Treatment Outcome Profile (a 28-item validated tool for drug and alcohol outcome measures including substance use, and social and wellbeing indicators). Self-report data will be verified by urine drug screens collected at baseline, mid-treatment and end of treatment.

The impact of TMS on specified cognitive domains is assessed by two cognitive tests done at baseline and end of treatment. These are the Go/No-Go test examining response inhibition (inhibitory control), and a cue reactivity paradigm (assessing reactivity of craving measured with a visual analogue scale, to drug and non-drug cues using a validated MA and neutral image database).

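### The withdrawal text both invites participants who stop TMS to stay in the research assessments and says that no further information is collected from them; the final assessment also has two anchors that disagree for early stoppers

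*Protocol article*

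**What the plan says.** All the withdrawal wording at issue is in the protocol article, mostly in the closing paragraph of the Study schedule section.

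- On leaving TMS: "Participants who withdraw from the TMS component of the study will be invited to continue completing the research component of the study".
- On the participant's own decision to stop, at the end of the same paragraph: participants may "stop treatment or revoke their consent at any time without giving a reason and no further information would be collected".
- Just after Table 1, the definition of study completion names a further status, being "prematurely withdrawn from the entire study (i.e. treatment and research visits").
- Two involuntary routes out are described. The Intervention section says that "participants will be withdrawn if they are unable to tolerate treatment at 70% of the RMT" at the end of the third treatment day. The Study schedule section adds, besides an unresolved device-related event, the case where "they miss more than 6 (of 12) study TMS sessions".
- Table 1 heads the last visit "Final assessment (day 28) within 7 days of last treatment".
- On patient experience, the Outcome measures section says: "A semi-structured questionnaire of patient experience will be administered post-treatment". Table 1 schedules it at the final assessment only.

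**The concern.** A participant who decides to stop TMS falls under both sentences. One leads to an offer of continued assessment and the other to no more data. Staff at different sites, or the same staff on different days, could apply either.

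What is at stake is everything measured after stopping: later Timeline Follow Back weeks, the mid-treatment and final urine screens, craving scores, the final Go/No-Go and cue tasks, the patient-experience questionnaire, and adverse events that emerge after stopping. The Sample size section says that the trial is meant to inform a larger study on drop-out, adherence and completion, and to give preliminary efficacy data. If stoppers contribute nothing after they stop, the end-of-treatment and patient-experience summaries describe mainly those who stayed. Data never collected cannot be recovered at analysis.

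The final visit adds a smaller problem. Its two anchors describe the same visit for someone treated into week 4, but different visits for someone who stops earlier.

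**Working it through.** The plan gives no figure to reproduce: the sample size is pragmatic and no drop-out rate is stated. The check is a comparison of the text, with short arithmetic for scale.

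**1. Do the two sentences collide?** Take a participant who chooses to stop TMS but does not revoke consent.

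| Rule | Research assessments afterwards |
|---|---|
| Invitation sentence | Offered |
| Last sentence of the paragraph, read literally | None |

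The last sentence joins stopping treatment and revoking consent with *or*, and puts no limit on the clause that ends data collection. The completion definition treats leaving both treatment and research visits as a status of its own, so treatment-only withdrawal is evidently meant to differ. The last sentence removes that difference, and nothing else in the article restores it.

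**2. What survives under either sentence?** Referrals, eligibility, consent, sessions attended up to stopping, the number of drop-outs, and the weekly Timeline Follow Back and craving data collected before stopping.

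**3. What is lost under the literal reading?** The post-stopping measures listed above. Of the items under the Primary outcomes heading (referrals, eligibility and consent, adverse effects), only adverse events after stopping are exposed.

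**4. Scale.** With 15 per arm and 30 in all:

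- One person lost = 1/15 = 6.7% of an arm, or 1/30 = 3.3% of the whole sample.
- If k of 15 are lost, a reported proportion differs from the full-arm proportion by (k/15) × (completer proportion − stopper proportion). Since the bracket cannot exceed 1 in size, the distortion is at most k/15: 6.7 points for k = 1, 20 points for k = 3 and 40 points for k = 6. These values of k are assumptions.
- The same expression with means applies to days of use or craving. The documents give neither k nor the difference between completers and stoppers, so the actual value may be anywhere from zero up to the bound.

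**5. The final-visit anchor.** If the last treatment is on day d, the seven-day rule puts the visit no later than day d + 7. Day 28 satisfies both only if d + 7 ≥ 28, that is d ≥ 21. Table 1 places week 4 at days 22 to 27, so in practice the anchors agree for those treated into week 4 and conflict for nearly everyone who stops before it. As an assumed example, with d = 5 the visit is due by day 12. A 28-day recall ending then covers 12 trial days and 28 − 12 = 16 days before treatment began. At d = 15 the limit is day 22, and 28 − 22 = 6 days fall before treatment.

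**The case against.** The best defence is that the intent can be recovered. The article distinguishes leaving TMS from leaving the whole study, so the loose final sentence was probably written with full withdrawal in mind, and the repair is one clause. The article is also a condensed text, and the full protocol is not shown. This makes the problem narrow but does not remove it. The conflict is between two statements that the article makes, not a detail it leaves out.

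Several stronger readings are tempting, and here the defence is right.

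- *That the main feasibility results are lost.* They are not; the counts in step 2 survive.
- *That a primary outcome is compromised because acceptability is primary.* The abstract does say "Primary outcomes are feasibility measures including recruitment, retention and acceptability of the intervention", but the Trial objectives section and the Secondary outcomes section both place patient experience among the secondary items. Adverse events after stopping are the only exposed part of the primary set as analysed.
- *That the loss would favour active TMS.* A reader might suppose that intolerance falls mainly on the active arm and that heavier users leave. The documents do not show either. Sham also delivers scalp sensation (Control and blinding), intensity can be lowered for discomfort (The intervention), and discontinuation for the common side effects is described as low. Arm summaries are descriptive, with no formal comparison.
- *That the unqualified use of withdrawn in the intolerance and missed-session rules is a separate defect.* What it covers is detail that the full protocol may settle.

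On the anchor, the defence notes that the seven-day rule would bring the experience questionnaire to early stoppers soon after they stop. That is fair, but it works only if they are assessed at all, and it moves their other end-of-treatment measures away from day 28.

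**Conclusion.** The contradiction is real and stands in the current text. Read literally, the last sentence ends outcome and adverse-event collection for participants who stop TMS without revoking consent, against the invitation earlier in the same paragraph. The end-of-treatment and patient-experience summaries would then lean towards completers. Recruitment, attendance, drop-out counts and data gathered before stopping are unaffected.

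The size is limited to 6.7% of an arm per person lost. Anything beyond that, including the direction between arms, depends on drop-out rates and on differences between stoppers and completers that the documents do not give. The conclusion also assumes that at least some participants stop TMS early and that staff apply the last sentence as written. If all staff follow the invitation sentence and participants accept, the loss disappears.

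The anchor conflict is secondary and concerns only those whose last treatment is before day 21. Overall this should be fixed because the remedy is cheap. It is not a flaw that defeats the trial's purpose.

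**What to change.** Reconcile the two sentences:

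1. Apply the no-further-information clause only when a participant revokes consent to research.
2. State that anyone who stops TMS for any reason, including involuntary withdrawal, is invited to continue the scheduled assessments and adverse-event recording. Table 1 ties the weekly assessments to the first session of each week, so say when they fall for someone with no sessions.
3. Give the final assessment one anchor for everyone, namely day 28 from first treatment with a stated window, whatever the date of last treatment.

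The rules on when TMS is stopped are left as they are; only the data collection that follows is addressed.

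The cost is rewording of the protocol and consent form, and some additional follow-up of people who have stopped. Reminder messages and calls are already planned, but urine screens and vital signs need attendance, so telephone contact will not cover everything. Some stoppers will decline, and their outcomes will still be missing.

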### Termination

The Principal Investigator or Trial Management Committee may recommend stopping the trial should the number and/or severity of adverse events justify discontinuation of the study.

## Study assessments

### Safety

#### Safety event reporting

Information will be collected on standard adverse events and serious adverse events (SAE) with relevant data reported to the ethics committee and regulatory authorities as required by the study protocol and ethics approval. The study management committee will review interim safety data at regular intervals.

### Side effects of TMS/TBS [25, 40]

#### Common side effects

Local pain, discomfort, headache and neck pain—all generally mild, discontinuation rates due to these symptoms are low. Pain is thought to be due to stimulation of superficial nerves or facial muscles, neck pain related to uncomfortable positioning during treatment, and headache may relate to local scalp stimulation [40].

#### Severe side effects

The risk of seizures is very low with the incidence thought to be equivalent to the incidence of spontaneous seizures with antidepressant therapy (0.1–0.6%) [25, 40]. The risk is increased with high-frequency treatment and more intense treatment protocols; pre-existing neurological conditions, adolescent patients, substance use and concurrent medication changes may all impact the seizure threshold. The risk of TMS-induced hearing impairment is also very low [25]. Studies have found that when adequate hearing protection is used, no change in hearing after a course of TMS is seen. We mitigate this risk by the use of approved hearing protection (earplugs); prompt referral for auditory assessment of all individuals who complain of hearing loss, tinnitus, or aural fullness following completion of TMS; and excluding those with pre-existing hearing disorders from the study.

The study will utilise the safety guidelines published in the Australian Psychiatry “transcranial magnetic stimulation (TMS) safety: a practical guide for psychiatrists” [40]. In the unlikely event that a participant has a seizure during a treatment session, a standard protocol for managing seizures in outpatient clinic settings will be utilised.

#### Data management and analysis

All data collected for the study will be confidentially managed and stored using Research Electronic Data Capture (REDCap) data capture tools [41, 42] (refs). REDCap is a secure, web-based application designed specifically for research studies, hosted by Hunter New England Local Health District. The study investigators and study team will have access to the study data. The study management team will oversee data monitoring.

As a pilot study, data will be summarised by descriptive statistics for primary and secondary outcome measures. Outcomes will be summarised across the intervention and control arms of this study.

#### Primary outcomes

Feasibility will be assessed via reporting the number of study referrals, the proportion deemed eligible and consenting (*N* (%)). Safety will be assessed by reporting the number of adverse effects (*N*).

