### Trial objectives and endpoints

The primary objectives are as follows:

Assess the feasibility and preliminary safety of using TMS for the treatment of moderate to severe MA use disorder in outpatient drug and alcohol settings.

The secondary objectives are as follows:Examine treatment adherence rates of participants for the use of TMS and counselling for MA use disorderAssess the impact of TMS on substance use in patients with MA use disorderAssess the impact of TMS on cravings in patients with MA use disorderAssess the impact of TMS on cognition in patients with MA use disorderAssess patient experiences with the use of TMS for MA use disorder

N.b. The study is not powered for testing differences between arms. Reporting the impact of TMS on substance use, cravings and cognition will be descriptive and exploratory in nature.

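### Preliminary safety, a primary objective, is to be summarised as a bare count of adverse effects, with no count of participants affected and no clear statement that it is by arm

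*Protocol article*

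**What the plan says.** The primary objective in Trial objectives and endpoints is to "Assess the feasibility and preliminary safety of using TMS for the treatment of moderate to severe MA use disorder in outpatient drug and alcohol settings". Under Primary outcomes, the analysis section turns the safety half of this into one measure: "Safety will be assessed by reporting the number of adverse effects", with N as the only statistic. The sentence before it, on feasibility, specifies N (%).

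Two statements introduce both outcome sections under Data management and analysis: "data will be summarised by descriptive statistics for primary and secondary outcome measures", and "Outcomes will be summarised across the intervention and control arms of this study". Under Secondary outcomes, the treatment group is then named for adherence, self-reported use, urine screens, craving and cognition. It is not named for patient experience, and it is not named for safety under Primary outcomes.

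The abstract ranks safety differently: "Secondary outcomes include monitoring of safety and preliminary efficacy data". The objectives and the analysis section agree with each other that it is primary, and I have followed them.

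**The concern.** An event count answers how many events were logged. A safety objective, even a preliminary one, mainly asks how many of the people treated had a problem. The two part company when events recur within a person, and here they probably will. The article expects mostly mild local pain, headache and neck pain, gives treatment on up to 12 days with three paired stimulation cycles each day, and keeps an adverse event log throughout.

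Exposure will also differ between participants. They can be withdrawn for intolerance after the third treatment day or for missing more than 6 of 12 sessions, so the number randomised is not automatically the right denominator.

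The arm matters because the sham is not physically inert. Its scalp electrodes deliver 2 to 5 mA and are active only in sham sessions, so sham participants can have local effects of their own. A count over both arms would add these to the effects of TMS.

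At stake is how useful the pilot is for its stated purpose of informing a larger trial. That trial's designers will want the proportion of participants affected, and a bare N does not supply it.

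**Working it through.** **The plan's own figure.** The article gives no event rate, precision target or power calculation for safety. The only figure to reproduce is the arm size: 30 participants at 1:1 is 30/2 = 15 per arm, which agrees with Sample size.

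**Inputs from the article.** 15 per arm (Sample size); 12 treatment days with three paired cycles each, so up to 12 × 3 = 36 cycles per participant (The intervention). The count of 12 events below is my assumption, for illustration only.

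**Step 1: what N = 12 says about participants in one arm.** If E events are logged, the number of participants affected can be anything from 1 to the smaller of E and 15. With E = 12:

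| Pattern behind N = 12 | Participants affected | Exact 95% CI |
|---|---|---|
| All 12 events in one person | 1/15 = 6.7% | 0.2 to 31.9% |
| One event in each of 12 people | 12/15 = 80% | 51.9 to 95.7% |

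The intervals are Clopper-Pearson. For x of n, the lower limit is the 2.5% quantile of Beta(x, n − x + 1) and the upper limit is the 97.5% quantile of Beta(x + 1, n − x). The two intervals do not overlap, yet the planned summary prints the same number for both patterns.

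**Step 2: what a pooled N = 12 says about arms.** The split between active and sham could be 12 and 0, 6 and 6, or 0 and 12. A single total cannot tell these apart.

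**Step 3: how the arm is specified.** The rule in Data management and analysis covers primary as well as secondary outcomes, and summarising *across* two arms can mean each arm in turn or the two combined. Secondary outcomes removes the doubt for most measures by naming the treatment group. The safety line does not.

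**Step 4: reading a zero.** For x = 0 the exact two-sided upper limit is 1 − 0.025^(1/n).

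- n = 15: 1 − 0.025^(1/15) = 21.8%
- n = 30: 1 − 0.025^(1/30) = 11.6%

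A category with no events in 15 active participants is compatible with a true risk of up to about one in five. This limit comes from the sample size and not from the table layout. It is a reason to print the interval, not a measure of the flaw.

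**The case against.** The strongest reply is that this is a condensed article about a descriptive pilot. The layout of adverse event tables, the safety population and the choice of intervals normally sit in a full protocol or analysis plan, neither of which is shown. No outcome here has an interval, and formal comparison between arms is expressly ruled out. Much of this stands: the absence of intervals is not a defect in itself, and the interval is only a preference. It does not cover the summary measure, however. The article chooses a statistic for each outcome, and for safety it chooses N where the adjacent feasibility line has N (%). That is a stated choice.

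A reader might also infer several stronger points that the documents do not support:

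- **That safety will be pooled over arms.** Nothing says so. The general rule is ambiguous, and patient experience also lacks the treatment-group wording, so the omission is not peculiar to safety.
- **That the trial cannot show anything about TMS against sham.** Counts by arm at 1:1 would allow a crude descriptive contrast, and the trial disclaims more than that. With assumed risks of 20% and 40%, power at 15 per arm is only about 22% (two-sided 5%), so better tabulation would not make this a comparative safety study.
- **That serious and mild events will be lumped together in the data.** Safety event reporting collects serious events as a category, and the withdrawal criteria rely on severity and device-relatedness. The information appears to be collected; the summary line does not use it.
- **That the low chance of seeing a seizure counts against the plan.** At the quoted incidence of 0.1 to 0.6%, the chance of at least one seizure in 15 is 1 − 0.999^15 = 1.5% to 1 − 0.994^15 = 8.6%. This follows from n = 15 however safety is tabulated.
- **That medication changes go unrecorded during treatment.** Severe side effects notes that "substance use and concurrent medication changes may all impact the seizure threshold", and the Table 1 row "Concomitant medications" is marked only at screening and baseline. Table 1 also shows TMS safety screening three times in each treatment week. Its content is not shown, so no gap can be claimed.

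**Conclusion.** The point holds in a limited form. The measure fixed for the safety part of a primary objective has no participant-level numerator or denominator, and the article does not make clear that it will be given by arm. Followed literally, it prints the same N for an arm in which 6.7% were affected and one in which 80% were. Those two percentages are the extremes for an assumed count of 12 in an arm of 15; the real ambiguity depends on how often events recur within a person, which the article does not estimate. The conclusion rests on recurrence being likely, given the expected effects and the number of treatment days, and on taking safety as primary, as the objectives and analysis section do.

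This is a weakness in reporting, not a threat to the trial's validity. It can be put right without changing the design or the data collected.

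**What to change.** Reword the safety line under Primary outcomes so that it reports, for each arm and among participants who received at least one session:

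- the number and percentage with at least one adverse event;
- the number and percentage with at least one device-related adverse event;
- the number and percentage with any serious adverse event;
- the total number of events, as now planned.

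Preferably give each percentage an exact 95% interval, so that a zero appears with its upper limit (21.8% for 0/15) and is not taken as evidence of safety. Bring the abstract's ranking of safety into line with the objectives in the same edit.

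The cost is one descriptive table from the existing adverse event log, and a more cautious safety statement at the end. No between-arm test and no additional medication form is needed.
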